### Sample size

In our previously performed retrospective study the incidence of a superior cosmetic result, without intervention, was 71%. An improvement of superior cosmetic outcome to 85% was considered clinically relevant. Expected clinical relevant difference is a 14% improvement in the incidence of a superior cosmetic result as evaluated by an independent panel. The sample size calculation is based on comparing two proportions in independent groups by the Chi-Square test. With 80% power and 5% significance level we need a study population of 240 patients (120 in each arm). There is a possibility that even after randomization the patient can still undergo mastectomy instead of BCS. We expect this for less than 25% patients in each arm, therefore we aim to include 300 patients in total (150 in each arm).

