**Methods/design:**

Multicentre, single-blinded, randomized controlled trial comparing standard preoperative work-up to a preoperative work-up with addition of the prediction model. Tumour volume to breast volume ratio and tumour location in the breast will be used to predict cosmetic outcome in invasive breast cancer patients opting for BCS. Three dimensional (3D)-ultrasonography will be used to measure the tumour volume to breast volume ratio needed for the prediction model. Sample size was estimated based on a 14% improvement in incidence of superior cosmetic result one year after BCS (71% in the control group versus 85% in the intervention group). Primarily cosmetic outcome will be evaluated by a 6-member independent panel. Secondary endpoints include; (1) patient reported outcome measured by BREAST-Q, EORTC-QLQ-C30/BR23 and EQ-5D-5 L (2) cosmetic outcome as assessed through the BCCT.core software, (3) radiation-induced reaction (4) surgical treatment performed, (5) pathological result and (6) cost-effectiveness. Follow-up data will be collected for 3 years after surgery or finishing radiotherapy.

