## Methods/design

### Trial design

This single-blinded, multicentre, randomised controlled trial targets women with the diagnosis of primary breast cancer. Patients will randomly be assigned (1:1) to either the intervention or control group after written informed consent is given. The study is in compliance with the Helsinki declaration. Ethical approval has been granted by the Institutional Review Board of the Erasmus University Medical Centre, Rotterdam, the Netherlands (reference-number: MEC-2013-360). This trial is registered before the start of the inclusion on February 17th, 2015 (NTR 4997). Figure 1 present a flow-diagram of the trial design.

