### Data collection and statistical analysis

#### Primary study parameter

Cosmetic outcome is calculated by obtaining the mean score for all panel members. The score per panel member is based on the mean score off the 11 scored items combined. Subsequently, the mean panel evaluation will be dichotomized by defining a mean of <1.5 as superior and a mean of >1.5 as inferior. The primary outcome is the incidence of a superior cosmetic outcome in both arms. Difference will be evaluated by using the Chi-square analysis (if normally distributed) or the non-parametric Kruskal-Wallis test (if not normally distributed).

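### 120 patients per arm give about 75% power, not 80%, for 71% versus 85% at a two-sided 5% level; 80% needs 137 per arm

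*Protocol article*

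**What the plan says.** All inputs are in the protocol article.

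- Control rate (Sample size), from the group's retrospective study: "the incidence of a superior cosmetic result, without intervention, was 71" per cent.
- Target (Sample size): "An improvement of superior cosmetic outcome to 85% was considered clinically relevant". The abstract's Methods/design paragraph repeats the pair: "71% in the control group versus 85% in the intervention group".
- Method (Sample size): "The sample size calculation is based on comparing two proportions in independent groups by the Chi-Square test".
- Result (Sample size): "With 80% power and 5% significance level we need a study population of 240 patients (120 in each arm").
- Allowance for mastectomy after randomisation (Sample size): "We expect this for less than 25% patients in each arm, therefore we aim to include 300 patients in total (150 in each arm").
- Allocation (Trial design): "Patients will randomly be assigned (1:1) to either the intervention or control group".
- Primary test (Primary study parameter): "Difference will be evaluated by using the Chi-square analysis (if normally distributed").

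The article does not say whether the 5% is one- or two-sided, and it mentions no continuity correction.

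**The concern.** The two rates, the test, the level, the power and the allocation ratio fix the sample size once the test is taken as two-sided. The printed result is clearly smaller than these inputs produce. This is not a detail left to a fuller document, because the inputs and the result stand in the same paragraph and disagree.

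This is the article's only power statement for the primary endpoint. If it is wrong, the trial is more likely than stated to miss the difference its authors call clinically relevant, and a null result would be read against a power the trial did not have.

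**Working it through.** **Inputs.** p1 = 0.71, p2 = 0.85, difference d = 0.14, mean rate 0.78, equal arms, alpha 0.05, power 0.80 (z = 0.8416). Two-sided alpha gives z = 1.96; one-sided gives 1.645.

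**Attempt to reproduce 120.** Pooled chi-square formula, two-sided:

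n = [1.96·√(2·0.78·0.22) + 0.8416·√(0.71·0.29 + 0.85·0.15)]² / 0.14²

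= [1.96·0.5858 + 0.8416·0.5774]² / 0.0196 = (1.1482 + 0.4860)² / 0.0196 = 136.25, so **137 per arm**, 274 in total.

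Continuity correction: n' = (n/4)·[1 + √(1 + 4/(n·d))]² = (136.25/4)·[1 + √1.2097]² = 150.2, so 151.

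| Method, 80% power, 71% vs 85% | n per arm |
|---|---|
| Two-sided, pooled | 137 |
| Two-sided, unpooled | 134 (133.5) |
| Two-sided, arcsine | 135 (134.2) |
| Two-sided, continuity-corrected | 151 (150.2) |
| One-sided, pooled | 108 (107.2) |
| One-sided, continuity-corrected | 122 (121.07) |

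No two-sided method gives 120. One-sided without correction does not either. The last row comes close, but needs two unstated choices.

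**Another possible source.** A contrast of 70% versus 85%, two-sided and uncorrected, gives 120.5, so 121. The control rate may have been rounded, but the article states 71% in both the abstract and the Sample size section.

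**Power with 120 per arm, two-sided.** z = (0.14·√120 − 1.96·0.5858) / 0.5774 = (1.5336 − 1.1482) / 0.5774 = 0.667, so power = **74.8%**. Other versions: unpooled 75.7%, arcsine 75.5%, exact enumeration of the uncorrected test 75.5%, exact with Yates correction 70.2%. At 137 per arm the formula gives 80.2% and exact enumeration 80.9%.

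**Size of the gap.** 137 − 120 = 17 per arm, 34 in total. With 120 per arm, 80% power needs an intervention rate of 85.8%, a gain of 14.8 points instead of 14.

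**Effect of the 150 randomised per arm (two-sided, uncorrected).**

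| Evaluable per arm | Loss from 150 | Power, formula | Power, exact |
|---|---|---|---|
| 150 | 0% | 83.7% | 84.1% |
| 137 | 8.7% | 80.2% | 80.9% |
| 120 | 20% | 74.8% | 75.5% |
| 113 (150·0.75 = 112.5) | 25% | 72.2% | 72.7% |

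So 80% is kept only if at most about 9% of each arm drop out of the primary analysis.

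**The case against.** The strongest reply is that the article never says two-sided. Its Objective is worded as an improvement, and a one-sided 5% test with continuity correction has exact power of 80.2% at 120 per arm. That variant would support the stated figure. But the chi-square test named for both the sample size and the primary analysis is ordinarily non-directional, and nothing in the text mentions a one-sided test or a correction. What stands is that the criticism must be labelled two-sided, and that the sponsor can be asked which calculation was run.

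The second reply is that 240 is an intermediate figure: 300 are randomised, and 150 per arm exceeds 137. This holds only if nearly everyone is evaluable. The Sample size section adds the extra 60 patients to cover mastectomies, so they are a loss allowance and not spare power. It is fair, though, to confine the proven error to the 120-per-arm statement: expected loss is given only as under 25%, so the power of the whole design is conditional.

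The third reply concerns scale. The gap is about five power points, or less than one percentage point in the detectable rate, and the 71% comes from a single retrospective study. The error biases no estimate and does not raise the type I error. All of this is true and bears on how serious the error is, but the number remains wrong.

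**Conclusion.** The statement is wrong as written. For 71% versus 85% with a two-sided 5% chi-square test, 80% power needs 137 evaluable patients per arm, and 120 give about 75% (about 70% if Yates correction is applied). The type II error at the stated size is about 25% instead of 20%.

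This rests on one assumption the article does not state, two-sidedness, and on taking its rates of 71% and 85% at face value. The abstract repeats only the rates; it gives no sample size or power and needs no separate correction. Whether the 300-patient trial reaches 80% depends on how many patients enter the primary analysis.

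**What to change.** Correct the Sample size paragraph to say that the test is two-sided at 5%, that 80% power for 71% versus 85% needs 137 evaluable patients per arm, and that 120 per arm give about 75%. If another calculation was used (one-sided with continuity correction, or a control rate of 70%), state it and justify it.

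Then choose one of two courses:

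- **Keep 300.** State the power for the number expected in the primary analysis: about 84% if all 150 per arm are included, about 75% at 120, and about 72% at 112 to 113 if the 25% ceiling is reached.
- **Keep 80% power after losses.** Randomise 137/0.80 = 171.25, so 172 per arm (344 in total) for a 20% loss, or 137/0.75 = 182.7, so 183 per arm (366 in total) for a 25% loss.

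The first course costs one rewritten paragraph and a less favourable power figure. The second costs 44 to 66 more patients. The Discussion reports only the first 30 inclusions, so either was still feasible at that stage.

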#### Secondary study parameters

Cosmetic result assessed by the patient (BREAST-Q), cosmetic evaluation through BCCT.core and radiation-induced reaction (RTOG/EORTC) will be analysed by comparing the intervention and control group. For normally distributed categorical data, the Chi-Square test will be used and the Kruskal Wallis test if not normally distributed. Continues variables as the Q-score will be analysed making use of the Student T-test if normally distributed or Mann-Whitney U test if not normally distributed. Pathological result will be analysed by comparing the percentages of incomplete tumour excisions and mean lumpectomy specimen size between the two study arms. The secondary study parameters will be analysed based on the intention-to-treat principle (i.e. including the patients treated with mastectomy). Surgical strategies performed will be analysed by comparing the percentages of the different types of surgery performed by using a Chi-square analysis if normally distributed or Kruskal-Wallis test if not normally distributed. Patients’ quality of life, conducted through the EORTC questionnaire/Euro-QoL and BREAST-Q questionnaires will be presented in a quantitative manner. Cost-effectiveness will be calculated by Markov modelling using ‘Quality-Adjusted Life Years’ (QALY’s).

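### Multiplying 120 by 1.25 to reach 150 per arm covers mastectomy loss only up to 20%; at the stated 25% bound about 112 per arm remain

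*Protocol article*

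**What the plan says.** All the inputs are in the Sample size section of the protocol article, except the allocation ratio, which is under Trial design.

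- Control rate, from the group's retrospective study, in per cent: "the incidence of a superior cosmetic result, without intervention, was 71".
- Target rate: "An improvement of superior cosmetic outcome to 85% was considered clinically relevant".
- Test: "comparing two proportions in independent groups by the Chi-Square test".
- Evaluable number: "With 80% power and 5% significance level we need a study population of 240 patients (120 in each arm". Whether the 5% is one-sided or two-sided is not stated.
- Allowance for patients who have a mastectomy after randomisation: "We expect this for less than 25% patients in each arm, therefore we aim to include 300 patients in total (150 in each arm".
- Allocation: "Patients will randomly be assigned (1:1) to either the intervention or control group".

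The section on secondary study parameters adds: "The secondary study parameters will be analysed based on the intention-to-treat principle (i.e. including the patients treated with mastectomy". The primary study parameter has no matching sentence.

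**The concern.** The section moves from 120 to 150 per arm and presents the larger number as the consequence of the 25% allowance. An allowance for loss has to be divided out, because the loss applies to the patients randomised and not to the patients left over. Multiplying by 1.25 gives a number that, after a 25% loss, falls below the 120 it was meant to protect.

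At stake is whether the recruitment target delivers the evaluable number that the plan itself asks for, and what power is left for the primary comparison if the loss comes near the stated bound.

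**Working it through.** **Inputs.** Control rate p1 = 0.71, intervention rate p2 = 0.85, difference d = 0.14, 120 evaluable per arm, loss below 25% per arm, 150 randomised per arm, 1:1 allocation. Assumed, because not stated: two-sided 5% and no continuity correction.

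**Step 1: reproduce the planned figure.** 120 × 1.25 = 150, an exact match. Division gives 120 / (1 − 0.25) = 160 per arm, or 320 in total, which does not match.

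**Step 2: what 150 per arm leaves.**

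| Mastectomy loss | Remaining per arm |
|---|---|
| 20% | 150 × 0.80 = 120 |
| 22% | 150 × 0.78 = 117 |
| 25% | 150 × 0.75 = 112.5 |

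The largest loss that keeps 120 is 1 − 120/150 = 20%. Steps 1 and 2 do not depend on the test or its sidedness.

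**Step 3: power.** For n per arm, with the pooled-variance chi-square,

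power = Φ{ [d√n − 1.96 √(2 p̄(1 − p̄))] / √(p1(1 − p1) + p2(1 − p2)) }, where p̄ = 0.78.

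Here √(2 × 0.78 × 0.22) = 0.5858 and √(0.2059 + 0.1275) = 0.5774.

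- n = 112: (0.14 × 10.583 − 1.1482) / 0.5774 = 0.577, so power is 71.8%. Exact enumeration of the same test gives 72.2%, and the unpooled variance gives 72.8%.
- n = 120: (0.14 × 10.954 − 1.1482) / 0.5774 = 0.667, so power is 74.8% (exact 75.5%).

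**Step 4: number needed for 80%.** n = (1.96 × 0.5858 + 0.8416 × 0.5774)² / 0.14² = 136.3, so 137 per arm.

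**Step 5: split the shortfall at the bound.** From 80% to 74.8% is about 5 points and belongs to the base of 120. From 74.8% to 71.8% is 3 points and belongs to the inflation step. Correcting the inflation alone, to 160 per arm, would restore 120 evaluable at 25% loss but only 74.8% power.

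**Step 6: sensitivity to the unstated choices.**

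| Test | Needed per arm for 80% | Power at 112 |
|---|---|---|
| Two-sided, uncorrected | 137 | 71.8% |
| Two-sided, continuity-corrected | 151 | about 66% |
| One-sided, continuity-corrected | 122 | about 77% |
| One-sided, uncorrected | 108 | about 82% |

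Only the one-sided, continuity-corrected version comes near 120, and the article states neither of those features.

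**The case against.** **The 25% is a ceiling, not a forecast.** The text expects less than 25%. At any loss up to 20%, 150 per arm does leave 120, and the shortfall never exceeds 7.5 patients per arm. This stands, and it makes 112 the limiting case. However, the article gives no other loss rate, so the ceiling is the only figure to which the allowance can be held, and it is the one the text uses to justify 150.

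**The power loss is mostly not due to this step.** A reader might infer that the inflation step takes power from 80% to 72%. The article's figures do not support that: about 5 of the 8 points are lost already at 120 per arm. Even if 120 did give exactly 80%, 112.5 would still give about 77%.

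**Sidedness is assumed.** This also stands. Two-sided is the usual reading of a chi-square test at 5%, but the article does not say so. An uncorrected one-sided test would keep power above 80% at 112; it would also need only 108 per arm, so it does not explain the 120. The figure of 72% must carry its assumption.

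**Mastectomy patients might be analysed after all.** Their exclusion from the primary analysis is implied, not stated. The inflation makes sense only if they do not count towards the 120, and intention-to-treat is spelled out for the secondary parameters alone. A reader might also infer that analysing everyone randomised would recover the power at no cost. The documents do not support that. The Abstract and the Follow-up section tie the cosmetic result and its photographs to breast-conserving surgery, and the article gives neither a rate of superior result after mastectomy nor a rule for rating it. The assumption of 71% against 85% cannot simply be carried over. Who enters the primary analysis is a separate question.

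**Missing photographs.** A reader might expect these to reduce the numbers further. The article gives no rate, and a condensed article may leave attrition to the full protocol, so nothing is claimed here.

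**Conclusion.** The sample-size statement is wrong as written. With 150 per arm, the plan's own requirement of 120 is met only if mastectomy loss is at most 20%; at the stated 25% bound about 112 per arm remain, and 160 would be needed to keep 120. This part is plain arithmetic and rests only on mastectomy patients not counting towards the 120, as the allowance implies.

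On a two-sided 5% uncorrected chi-square for 71% against 85%, power at that bound is about 72%. The inflation step itself costs about 3 points, and only in full when the loss reaches 25%. The larger part of the gap to 80% comes from the base figure of 120, where 137 are needed. The error is modest in size, but it sits in a stated planning figure that does not deliver what the text claims for it.

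**What to change.** Restate the paragraph. It should say that 150 per arm keeps 120 evaluable patients only for a mastectomy loss of up to 20%, and that at 25% about 112 per arm remain, with about 72% power for 71% against 85% on a two-sided 5% chi-square test without continuity correction. State the sidedness explicitly.

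The cost is a few sentences of rewording, with no added patients and no change to the design. The restatement makes the numbers honest but does not restore 80% power. The base figure of 120 and the place of mastectomy patients in the primary analysis need to be settled separately.

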#### Follow-up

Three questionnaires will be obtained at all follow-up visits (i.e. ‘BREAST-Q postoperative modules’, the EORTC-QLQ-C30/B23 and the EQ-5D-5 L. Follow-up visits will be scheduled at 3 months (T1), 1 year (T2), and 3 year (T3) postoperatively. Photographs will be obtained both 1 and 3 year following BCS.

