## Discussion

The literature provides limited predictive factors for an expected favourable cosmetic outcome in breast cancer patients opting for BCS. To objectively device a tailor-made treatment plan this study makes use of a prediction model [10]. This study aims to provide level 1B evidence for the use of a preoperative prediction model for clinical decision making to improve cosmetic results in patients opting for BCS.

Following the inclusion of the first 30 patients (10%) the patients’ experiences tell us that the study is well accepted and appreciated. It is however of great importance that the study is discussed by the treating surgeon at the first or second consultation at the outpatient clinic. By the start of inclusion up to 40% of the approached patients declined participation. This was mainly based on too much burdening in the preoperative phase and an inadequate introduction of the study. If the treating surgeon introduces the study and explains the importance of the study in the preoperative phase the acceptance for participation is higher. With the allocation of multiple including centre’s in the region of Rotterdam the inclusion rate has adequately improved with an ongoing high acceptance of participating patients.

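### Enrolling 300 allows for mastectomy only: at the 25% ceiling it leaves 225 evaluable patients (about 72% power), at 20% exactly 240 (about 75%), with no margin for missing one-year photographs

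*Protocol article*

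**What the plan says.** The Sample size section of the protocol article gives a complete chain from effect to enrolment. The control rate of a superior cosmetic result is 71%, from an earlier retrospective study, and the target is 85%: "An improvement of superior cosmetic outcome to 85% was considered clinically relevant". The method is named: "The sample size calculation is based on comparing two proportions in independent groups by the Chi-Square test". The result follows: "With 80% power and 5% significance level we need a study population of 240 patients (120 in each arm"). The only reason given for enrolling more is that a randomised patient may still have a mastectomy: "We expect this for less than 25% patients in each arm, therefore we aim to include 300 patients in total (150 in each arm").

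The Abstract ties the sample size to the result one year after surgery. Under Primary outcome, the result is a panel rating made from photographs. The Follow-up section sets when they are taken: "Photographs will be obtained both 1 and 3 year following BCS". No rate of withdrawal, loss to follow-up or missing photographs appears anywhere in the article.

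**The concern.** The primary analysis can lose patients in two ways: by mastectomy, and by having no one-year photograph to rate. The margin of 60 patients is assigned wholly to the first. The second is in effect planned at 0%.

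The size of the margin is also a problem. An expected loss of up to 25% requires dividing by 0.75, and 300 does not meet that. Underneath both, 240 evaluable patients do not give 80% power under the usual two-sided reading of the stated test.

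At stake is how a null result will be read. A reader who accepts 80% will put the chance of missing a true 14-point benefit at 20%. In the scenarios discussed in the verdict it is about 25% to 33%.

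**Working it through.** **Inputs.** From Sample size: 71% versus 85%, chi-square test, 80% power, 5% significance, 120 per arm, mastectomy below 25%, 150 per arm enrolled. From Trial design: 1:1 allocation. Assumed here: a two-sided test (sidedness is not stated), mastectomy patients not evaluable for the primary outcome, and 5%, 10% or 15% missing photographs (the article gives no figure).

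**Step 1. The plan's 240.** With pooled rate 0.78, the null term is √(2 × 0.78 × 0.22) = 0.5858 and the alternative term is √(0.71 × 0.29 + 0.85 × 0.15) = 0.5774.

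n per arm = (1.960 × 0.5858 + 0.8416 × 0.5774)² / 0.14² = 136.3, so 137 per arm, 274 in total.

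The stated 240 is not reproduced. Other two-sided variants give 268 (unpooled), 270 (arcsine) and 302 (continuity correction). One-sided gives 216. Only one-sided with continuity correction comes close, at 244, and the article states neither feature.

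**Step 2. Power at 120 per arm.** Power = Φ[(0.14 × √n − 1.960 × 0.5858) / 0.5774]. At n = 120 this is Φ[(1.534 − 1.148) / 0.5774] = Φ(0.667) = 74.8%.

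**Step 3. From 240 to 300.** For a 25% loss, 240 / 0.75 = 320. The stated 300 equals 240 × 1.25. It also equals 240 / 0.80, the correct figure for a 20% loss. The article does not say how it was obtained.

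**Step 4. Evaluable patients and power from 300.** Evaluable total = 300 × (1 − mastectomy rate) × (1 − photograph loss). Power uses half of this per arm in the Step 2 formula.

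| Mastectomy | No photograph loss | 5% missing | 10% missing | 15% missing |
|---|---|---|---|---|
| 25% | 225 (72.0%) | 213.8 (69.8%) | 202.5 (67.4%) | 191.2 (64.9%) |
| 20% | 240 (74.8%) | 228 (72.6%) | 216 (70.2%) | 204 (67.7%) |
| 15% | 255 (77.3%) | 242.2 (75.2%) | 229.5 (72.9%) | 216.8 (70.4%) |
| 10% | 270 (79.6%) | 256.5 (77.6%) | 243 (75.3%) | 229.5 (72.9%) |

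Per arm, the 20% row is 120, 114, 108 and 102. At 25% mastectomy with 10% missing, about 101 per arm remain.

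**Step 5. Photograph loss that 240 can absorb.** Maximum loss = 1 − 240 / [300 × (1 − mastectomy rate)]. This is 0% at 20% mastectomy, 5.9% at 15% and 11.1% at 10%. At 25% the total is below 240 before any loss.

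**Step 6. When 300 gives 80%.** Step 1 needs 137 of the 150 per arm, so both losses together may not exceed 1 − 137/150 = 8.7%.

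**The case against.** The strongest reply is that the article gives a ceiling for mastectomy, not an estimate. At 10% or 15%, the 300 would cover 240 with some photograph loss. That stands. A reader might infer that any missing photograph takes the analysis below 240, but the documents do not support this. It is so at 20% mastectomy, where the margin is exactly zero. At 25% the shortfall comes before any photograph is lost, and clearly below 20% there is room. Even so, 25% is the only mastectomy rate the article names, and 300 does not hold there.

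A second reply is that missing photographs are being blamed for a deficit with another source. This also stands in part. About 5 points of the shortfall from 80% are present at 240 with complete follow-up. The part due to photograph loss at 20% mastectomy is about 2, 5 and 7 points for 5%, 10% and 15% missing, and it rests on assumed rates.

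A third reply is that a condensed article may leave attrition to the full protocol. That is fair for retention procedures, such as how photographs are sought from patients who stop questionnaires, and none is criticised here. It does not cover the sample size, because the article publishes the whole chain and attaches 80% to it.

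A reader might also take the Discussion's report that up to 40% of approached patients declined as evidence that attrition will be high. It is not. Those patients refused before consent, the burden was preoperative, poor introduction of the study was a second cause, and acceptance later improved.

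**Conclusion.** The point holds in limited form. The step from 240 to 300 covers mastectomy alone. From 300 randomised, 225 are evaluable at the 25% ceiling (about 72% power) and exactly 240 at 20% (about 75%), with nothing left for missing one-year photographs. With 10% of photographs also missing, power is about 67% and 70% respectively. Below 20% mastectomy some loss can be absorbed without falling under 240, but 240 itself gives about 75%, not 80%.

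This rests on three assumptions: a two-sided 5% test; mastectomy patients outside the primary analysis; and illustrative photograph losses of 5% to 15%. The second is inferred. The article promises intention-to-treat including mastectomy patients only for the secondary parameters, and the inflation makes sense only if they are not evaluable for the primary one. It would be too strong to say that the trial cannot reach 240 or that 300 can never give 80%, since the article's wording permits low mastectomy rates.

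**What to change.** In the Sample size section, state the assumed proportion of missing one-year photographs beside the assumed mastectomy rate. Then restate the evaluable number and power for 300 randomised with both applied, and stop quoting 80%. For example, with 20% mastectomy and 10% missing photographs: 150 × 0.80 × 0.90 = 108 per arm, about 70% power for 71% versus 85% at two-sided 5%. Giving the 25% case alongside it (about 101 per arm, about 67%) would show the range. State the sidedness and any continuity correction, so that the figure can be reproduced.

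The cost is a few sentences and a recalculation, with no extra patients. The downside is a less favourable power figure.
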